**Methods:**

A 2-armed, parallel randomized controlled trial was conducted between February 2022 and June 2022. Forty-eight children with autism (aged 7-12 years) were recruited from the Hainan Special Education School and randomly assigned to either a parental TTM or control group at a ratio of 1:1 based on random numbers generated with Online Research Randomizer. The generated sequences were concealed in an opaque envelope. Individuals in the parental TTM group received 16 parent-delivered TTM sessions over 8 weeks at the school’s health room after school, and the control group maintained a normal daily routine. Outcomes were assessed on admission, after 8 weeks, and at a 2-month follow-up and included the effect of massage treatment on autism symptoms, measured with the Autism Treatment Evaluation Checklist score (evaluated by parents and a blinded teacher), physiological parameters (ie, heart rate variability and gait), and the Parenting Stress Index, Fourth Edition–Short Form.

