### Ethical Considerations

This study complies with the ethical standards of the relevant national and institutional guidelines on human experimentation and was approved by the Khon Kaen University Ethics Committee for Human Research (HE642167). The study followed the Helsinki Declaration. Results will be published in a peer-reviewed journal and presented at domestic and international academic conferences to further promote communication. This protocol was registered with the Chinese Clinical Trial Registry (ChiCTR2100051355).

Researchers provided parents with information about the study and obtained informed consent from them while their children were in school. The parent or guardian signed the document and returned it to the school researcher or the teacher. Before the study, the parents were responsible for asking their children about their willingness to participate in the study. Children whose parents provided informed consent took part in the study. The researchers explained the study methods verbally to the children and parents and demonstrated the tests that would be performed on the children; the teachers and parents observed each child’s reaction to determine if the child consented or not before the test.

In the massage group, the participants were paid US $7 for each TTM session. In the control group, each volunteer participated in the evaluation 4 times and was paid US $7 each time. The decision was made that after data collection was finished, if good results were obtained in the parental TTM group, the control group would also be given training in TTM. Each teacher volunteer who participated in the 3 stages of assessment received US $30 for each stage.

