### Data Collection, Management, and Analysis

IBM SPSS (version 25; IBM Corp) will be used for data analysis. Missing outcome data will not be imputed in the analysis, but the multiple imputation method will be used to explore the potential impact of missing data on outcomes. Demographic data will be expressed as means with standard deviation and percentages. *P*<.05 will be considered statistically significant. Holm correction of *P* values will be applied for multiple comparisons to compare the immediate effects of TTM for autistic children and effects in the short and long term. The primary outcome is the ATEC score, which will use generalized estimating equations. Time will be the covariate and the model will include group, time, and the group × time interaction. A 2-tailed paired *t* test or Wilcoxon signed-rank test will be used to test ATEC score, HRV, and gait parameters, as well as PSI-4-SF score changes within each group after testing for normal distribution. The relationship between physiological effects and ATEC results will be evaluated using a correlation test. A coefficient value <0.4 indicates a low degree of correlation, a value between 0.4 and 0.7 indicates a medium degree of correlation, and a value >0.7 indicates a high degree of correlation between variables.

Two trained assessors will be responsible for data collection, electronic double entry of the data, and management of the database. A team from the Key Laboratory of Data Science and Smart Education at Hainan Normal University, which is independent of the study team, will be responsible for data monitoring.

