## Results

We finished all data collection on June 20, 2022. Data analysis will be started, and we expect results to be published in 2023. The normal distribution of the data will be determined before descriptive statistics for all variables are calculated. The participants’ demographic information will be reported as descriptive data. The primary outcomes will be expressed as continuous variables, and generalized estimating equations will be used to evaluate the effect of TTM on the children (via the ATEC score) at 3 time points: immediate, short term, and long term. Changes in physiological parameters (ie, HRV and gait parameters) after the intervention will be analyzed. Further, the relationship between ATEC score and physiological parameters will be identified with a correlation analysis. Finally, changes in parental stress throughout the intervention period will be investigated with the PSI-4-SF.

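### Time enters the primary ATEC model as a covariate; read literally, this is one slope per arm that nearly ignores the end-of-treatment score and cannot deliver the planned time-point comparisons

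*Protocol article*

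**What the plan says.** All places are in the protocol article.

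- **Data Collection, Management, and Analysis.** The primary ATEC analysis is a GEE: "Time will be the covariate and the model will include group, time, and the group × time interaction". The text does not say whether time is linear, continuous or categorical, and it names no primary visit or contrast. The software is given as "IBM SPSS (version 25; IBM Corp) will be used for data analysis". Holm correction "will be applied for multiple comparisons to compare the immediate effects of TTM for autistic children and effects in the short and long term".
- **Results.** The GEE is to evaluate the effect on ATEC "at 3 time points: immediate, short term, and long term".
- **Abstract, Methods.** "Outcomes were assessed on admission, after 8 weeks, and at a 2-month follow-up". Treatment is "16 parent-delivered TTM sessions over 8 weeks", and the trial was "conducted between February 2022 and June 2022".
- **Prior Work.** The first research question asks whether ATEC improves after the intervention compared with control. Instant effects are tied to gait and HRV, not to ATEC.
- **Ethical Considerations.** "In the control group, each volunteer participated in the evaluation 4 times", while teachers, who also rate ATEC, are paid for three assessment stages.

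**The concern.** In ordinary modelling language, and in the usual SPSS division of predictors into factors and covariates, a covariate is a continuous term. On that reading the model has one slope per arm, and the group × time term is one number: the difference in slopes.

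That shape suits this design poorly. Massage sessions stop at week 8, which is the middle visit, so any bend in the treatment effect is most likely there. A benefit present after 16 sessions that weakened over the untreated two months could leave the primary interaction test with little or nothing to detect.

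A single slope also cannot produce separate effects at several time points, so there would be nothing for the Holm correction to act on. Because the time labels are not tied to visits, it is not settled which comparison answers the primary question, and the choice could be made after the data are seen.

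**Working it through.** **Inputs from the article.** Visits at admission, week 8 and 2-month follow-up; 48 children randomised 1:1, so 24 per arm; 10% dropout; two-sided 5% level; 80% power.

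**Assumptions.** Follow-up is counted from the end of treatment, so it falls at about week 8 + 8.7 = 16.7 (range 16 to 17), which fits the February to June span. The within-child correlation r, the effect size and its course over time are not given in the article.

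**1. The plan's own figure.** The total of 48 cannot be reproduced, because no difference or SD is stated. It can only be inverted. With 24 × 0.9 = 21.6 completers per arm, d = (1.960 + 0.842) × √(2/21.6) ≈ 0.85. This is used below as an illustrative week-8 effect.

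**2. Weights in the slope.** For equally weighted visits, w = (t − t̄)/Σ(t − t̄)². At t = 0, 8, 16.7:
- t̄ = 24.7/3 = 8.233; deviations are −8.233, −0.233 and +8.467; the sum of squares is 139.5.
- w = −0.0590, −0.0017, +0.0607.
- Multiplied by the span of 16.7: −0.99, −0.03, +1.01.

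The GEE weights (X′R⁻¹X)⁻¹X′R⁻¹ under other settings, scaled the same way:

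| Visit times | Working correlation | Week-8 weight |
|---|---|---|
| 0, 8, 16 or coded 1, 2, 3 | independence, exchangeable, AR(1) | 0 |
| 0, 8, 16.7 | independence, exchangeable | −0.03 |
| 0, 8, 16.7 | AR(1), 0.5 to 0.7 | −0.05 to −0.06 |
| 0, 8, 17 | independence, exchangeable | −0.04 |
| 0, 8, 17 | AR(1), 0.5 to 0.7 | −0.07 to −0.09 |
| 0, 8, 16 | one assumed unstructured matrix (0.7, 0.5, 0.8) | −0.4 |

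**3. What the line would show at week 8.** Suppose the true group difference is 0 at baseline and 1 at week 8, and 0, 0.5 or 1 at follow-up. The least-squares line at t = 0, 8, 16.7 gives a week-8 difference of 0.33, 0.49 or 0.65. In the sustained case, part of the 0.65 is a spurious baseline difference: 0.667 − 0.0590 × 8.233 = 0.18.

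**4. Power at 24 per arm, visits at 0, 8, 16, exchangeable correlation.** The slope test is then the difference between arms in change from baseline to follow-up, with SE = √[(2/n) × 2(1 − r)]. For r = 0.7 this is √(0.0833 × 0.6) = 0.224.
- Sustained: 0.852/0.224 ≈ 3.81; power Φ(3.81 − 1.96) = 97%.
- Half kept: 0.426/0.224 ≈ 1.91; power Φ(1.91 − 1.96) ≈ 48%.
- Lost: the expected slope difference is 0; the rejection rate is 5%.

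| Effect at follow-up | Slope, r = 0.5 | Slope, r = 0.7 | Week-8 contrast, r = 0.5 | Week-8 contrast, r = 0.7 | 2-df test, r = 0.5 to 0.7 |
|---|---|---|---|---|---|
| lost | 5% | 5% | 84% | 97% | 87–98% |
| half kept | 32% | 48% | 84% | 97% | 76–94% |
| sustained | 84% | 97% | 84% | 97% | 87–98% |

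A simulation of 1,000 trials per profile (GEE, exchangeable, r = 0.7) gave 5.3%, 51.1% and 97.3% for the slope, against 97.3%, 96.6% and 97.1% for the week-8 contrast.

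**5. Time points side by side.** The schedule has admission, week 8 and follow-up. The GEE list has three labels, none called baseline and none defined. If the last two labels mean week 8 and follow-up, the first has no scheduled ATEC visit, since instant effects belong to gait and HRV.

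**The case against.** The strongest reply is that the straight line is inferred. The article never says linear, continuous or slope; authors often use *covariate* for any model term; and the article does not invoke the SPSS convention. The planned effects at three time points and the Holm correction make sense only with categorical time. This stands, and it means that a reader may not infer that the protocol commits to a linear trend. It does not remove the problem: the only sentence that defines the primary model points one way and the planned comparisons point the other.

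It can also be said that the coding of time belongs in a separate analysis plan. That would cover an omission. Here a term is stated, and following it literally gives a worse analysis.

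The size of the loss rests on assumptions, and nothing in the article says that the effect fades. If it is sustained, the slope test loses no power. Nor does the article plan to report a fitted week-8 value, so step 3 shows misfit and not an announced misreport. Near-zero weight is not universal either: the assumed unstructured matrix gave −0.4, although that sign would count a week-8 benefit against the slope.

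Finally, a reader might take the four control-group evaluations as contradicting the three-visit schedule. The text does not support that. The fourth may be an instant gait or HRV test, and the three teacher stages match the schedule.

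**Conclusion.** The point holds as a conflict in how the primary model is specified. Read literally, the model tests essentially follow-up minus baseline under independence, exchangeable or AR(1) correlation, and it cannot supply the visit-specific effects that the same section and the Results section plan. Categorical time was probably intended.

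It would go too far to say that the primary test will miss a real effect. With an assumed 0.85 SD and correlation 0.7, the literal model ranges from nearly no power (full fade), through about half (half fade), to no loss (sustained effect). At correlation 0.5 the half-fade figure is 32% against 84%.

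The gap in the time labels holds however *covariate* is read: baseline is absent, the labels are not mapped to visits, and no immediate ATEC visit is scheduled.

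**What to change.** The article says that data collection is complete and analysis has yet to start, so the change should be made and dated before outcome data are examined.

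1. State that time is a 3-level factor (admission, 8 weeks, 2-month follow-up) and that group × time is tested through visit-specific contrasts of change from baseline.
2. Name the primary test in advance. The group difference in change at 8 weeks, the end of treatment, is the natural choice. A 2-df group × time test followed by Holm-corrected contrasts is an acceptable alternative.
3. In the analysis and Results sections, map the time labels to the scheduled ATEC visits, include baseline, and keep *immediate* for gait and HRV.
4. In Ethical Considerations, add a note on what the fourth control evaluation is. Nothing more is needed there.

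The cost is a few sentences and one degree of freedom per arm (three means in place of an intercept and a slope). In the cases computed, the week-8 contrast has the same power as the slope test if the effect is sustained. It would have less than the slope test if the effect kept growing after treatment: 84–97% against about 100% for a doubling by follow-up.

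### The primary GEE names time as a covariate; read literally this gives one linear slope difference, which cannot supply the time-point-specific effects the article promises and leaves week 8 with almost no weight

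*Protocol article*

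**What the plan says.** The Data Collection, Management, and Analysis section of the protocol article sets the primary method: "The primary outcome is the ATEC score, which will use generalized estimating equations". The next sentence gives the model: "Time will be the covariate and the model will include group, time, and the group × time interaction". The software is fixed in the same section: "IBM SPSS (version 25; IBM Corp) will be used for data analysis".

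Two other statements say what the analysis should produce. The same section plans a Holm correction "to compare the immediate effects of TTM for autistic children and effects in the short and long term". The Results section says the GEE is used "to evaluate the effect of TTM on the children (via the ATEC score) at 3 time points: immediate, short term, and long term".

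The Abstract gives the schedule: "Outcomes were assessed on admission, after 8 weeks, and at a 2-month follow-up". The Intervention section places all 16 sessions within the first 8 weeks.

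**The concern.** The only sentence that specifies the primary model does not match what the model is meant to deliver. SPSS separates factors (categorical) from covariates (numeric, one slope each). Entered as a covariate, time yields a single 1-df group × time coefficient, hence one P value and no separate effect per visit. Holm would then have nothing from this model to correct.

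The shape matters too. Treatment stops at week 8, and a straight line through the treated and untreated periods fits neither a plateau nor a fade. This GEE is the only between-group comparison of ATEC that the article states; the paired t and Wilcoxon tests run within each arm. So the answer to the first research question, improvement compared with control, depends on how this sentence is carried out.

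**Working it through.** **Inputs from the article.** 48 children, 1:1, so 24 per arm; 10% dropout; 5% two-sided; 80% power; ATEC on admission, after 8 weeks and at a 2-month follow-up.

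**Assumptions, because the article gives no figure.**
- Follow-up is counted from the end of treatment, so it falls at week 16 to 16.7.
- The within-child correlation ρ is 0.5 to 0.7.
- The outcome SD is 1 at every visit.
- The effect size is back-solved. The article prints neither the SD nor the target difference, so its total of 48 cannot be reproduced. With 48 × 0.9 / 2 = 21.6 children per arm, a two-sample t test has 80% power for about 0.87 SD. That value is used as the week-8 effect d.

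**Step 1: weight of each visit in a linear slope.** The weights are w = (t − mean t) / Σ(t − mean t)².

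| Visit times | Admission | Week 8 | Follow-up |
|---|---|---|---|
| codes 0, 1, 2 | −0.5 | 0 | +0.5 |
| weeks 0, 8, 16.7 | −0.059 | −0.0017 | +0.061 |

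For equal spacing the slope is (follow-up − admission)/2, and week 8 drops out. Exchangeable and AR(1) working correlations also leave the week-8 weight at or near zero.

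**Step 2: the line fitted to the group difference.** Least squares on equally spaced visits gives:

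| True difference at the three visits | Fitted difference |
|---|---|
| 0, d, 0 (lost) | 0.33d, 0.33d, 0.33d |
| 0, d, 0.5d (half kept) | 0.25d, 0.50d, 0.75d |
| 0, d, d (kept) | 0.17d, 0.67d, 1.17d |

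When the effect is lost, the slope difference is zero and d/3 appears as a constant group difference. When it is kept, the slope test sees it, but the fitted change from admission to week 8 is 0.67d − 0.17d = 0.5d instead of d.

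**Step 3: power.** A between-arm difference in change has variance 4(1 − ρ)/n. For equal spacing, linear group × time tests the change from admission to follow-up, so its noncentrality is (share of d kept) × d / √(4(1 − ρ)/n). The week-8 contrast uses d itself. With n = 21.6:
- ρ = 0.7: √(1.2/21.6) = 0.236; 0.87/0.236 = 3.69, half of it 1.85.
- ρ = 0.5: √(2/21.6) = 0.304; 0.87/0.304 = 2.86, half of it 1.43.

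The noncentral t distribution then gives:

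| Effect at follow-up | Linear group × time (ρ 0.5 to 0.7) | Week-8 contrast (ρ 0.5 to 0.7) |
|---|---|---|
| fully kept | 80% to 95% | 80% to 95% |
| half kept | 29% to 44% | 80% to 95% |
| lost | 5% | 80% to 95% |

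**Step 4: check by simulated GEE** (24 per arm, week-8 effect 0.86 SD, ρ = 0.6, visits at 0, 8 and 16.7 weeks, 600 runs per case). If the effect is lost, linear group × time rejects in 6% of runs, the week-8 contrast in 93%, and Holm over the two visit contrasts in 89%. The group term of the linear model rejects in 22%, against 8% with no effect, so part of the effect surfaces as an apparent constant group difference. If half is kept, linear group × time rejects in 40% and the week-8 contrast in 93%.

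**The case against.** The strongest reply is that nobody has said time is linear. The section does not use the words slope, continuous or weeks, and clinical authors often call any model term a covariate. The Holm step and the stated purpose, "generalized estimating equations will be used to evaluate the effect of TTM on the children (via the ATEC score) at 3 time points", point to a categorical intent. A condensed article may also leave factor coding to a fuller plan. Much of this stands. A reader might infer that a straight line will certainly be fitted; the article does not support that. But the coding is not simply left out: the article states a role for time, in a plan that names SPSS, and that role conflicts with the planned outputs.

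A reader might also infer that week 8 never counts. That needs three ATEC visits at roughly equal spacing. The origin of the 2-month follow-up is not stated. Counted from admission (0, 8, 8.7 weeks), week 8 would have weight 0.45 on the scale where equal spacing gives −1, 0, +1, though a follow-up less than a week after the 8-week visit is hard to credit. The Ethical Considerations section mentions four evaluations for control children. If an extra visit near time zero entered the ATEC model, the week-8 weight would be 0.16. Those evaluations are not said to be ATEC visits, and the Abstract lists three.

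Finally, a reader might infer that any effect would be missed. That holds only for complete fading. A fully kept effect loses no power, and the article gives no evidence of which pattern to expect.

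**Conclusion.** The point holds as a conflict within the stated primary analysis. Taken literally, the covariate sentence defines a model that cannot produce the time-point effects promised elsewhere in the article. It is not established that the linear model is what will be run.

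If it is run on three roughly equally spaced visits, week 8 contributes almost nothing to group × time. The cost ranges from none in power (effect kept, but its week-8 size misfitted) through 29% to 44% against 80% to 95% (half kept) to 5% (lost). These figures rest on the assumed 0.87 SD, 21.6 children per arm and ρ of 0.5 to 0.7. The near-zero weight depends only on the number and spacing of visits. The sentence governs the only stated randomised comparison of the primary outcome, and according to the article analysis has not begun, so it should be settled first.

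**What to change.** Replace the covariate sentence with: *Visit (admission, 8 weeks, 2-month follow-up) enters the model as a three-level categorical factor with group and group × visit.*

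Report TTM minus control in change from admission at week 8 and at follow-up, each with a 95% CI. Then either name one of them (for example week 8) as the primary contrast, or apply the planned Holm correction across the two. State from which date the 2-month follow-up is counted.

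The cost is one sentence and one more interaction parameter, with no new data. Some power is lost if the effect really grew in a straight line to follow-up. With 24 per arm, an effect of 0.86 SD reached only at follow-up and ρ of 0.5 to 0.7, the 2-df group × visit test has 73% to 93%, against 83% to 96% for the linear term. A week-8 contrast alone would have 31% to 47% in that case, which should be weighed when choosing between a single primary contrast and Holm.

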Traditional Thai massage (TTM) is believed to have ancient origins and has 3 distinctive features: deep pressure massage, work on meridian (energy) lines, and stretching of the affected muscles and joints. TTM is widely used in health care [44,45] and rehabilitation [46,47]. The results of studies conducted to date suggest that TTM may facilitate immediate and short-term improvement in HRV [48,49] and some gait parameters in nonautistic patients [50,51]. Since an increase in HRV reflects a state of relaxation due to parasympathetic activity induced by TTM, patients either with or without autism can relax and reduce their restrictive-repetitive behavior patterns. Consequently, they should improve their gait pattern and speed. TTM has also been effectively used in the rehabilitation of children with disabilities by the Bangkok Foundation for Children with Disabilities [52]. However, we only found one study [53] that reported the effects of TTM administered by masseurs on autistic behavior, and its methodology and conclusions were questionable [54]. It appears that more research is needed to explore the effects of TTM on autism by using both subjective and objective evaluation.

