Furthermore, the refractory and lifelong nature of autism has profound implications for parents of autistic children and evidence shows that parents of children with autism experience more parenting stress than parents of nonautistic children or children diagnosed with other disabilities [55,56]. One recent review suggested that family-based interventions for mental disorders in children are becoming increasingly important, with more positive outcomes when parents are involved in the treatment [57]. Previous research revealed that parents who engaged in a massage-based intervention not only satisfied family-based care needs [58] but also showed relieved anxiety [42] and strengthened parent-child bonding [37,38,59]. The effects of TTM delivered by the parents of autistic children on these outcome measures have not been verified. This study aims to assess the effects of parental-delivered TTM in children with autism by evaluating changes in symptoms and physiological parameters (ie, gait and HRV). The primary objective of the study is to assess the effectiveness of parental TTM in improving symptoms of autism according to the Autism Treatment Evaluation Checklist (ATEC). Secondary objectives are to evaluate instant and cumulative effects of the parental TTM intervention via an assessment of gait and HRV and explore the relationship between symptom improvement and observed changes in physiological parameters. The tertiary objective is to examine changes in levels of parental stress after parents have administered the TTM intervention. The following four research questions will be addressed: (1) Do core symptoms significantly improve (ie, does ATEC score improve) in autistic children after parental TTM in comparison with the control group? (2) Do HRV and gait indicators significantly improve in children with autism after parental TTM? (3) Is ATEC score improvement related to observed changes in physiological parameters? (4) How does parental stress change throughout the intervention period, as measured by the Parenting Stress Index, Fourth Edition–Short Form (PSI-4-SF)?

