### Primary Outcome Measurement: ATEC

The ATEC questionnaire was developed by [name] and [name] M Edelson at the Autism Research Institute in the United States in the mid-1990s to help researchers and parents evaluate the effectiveness of various treatments for autistic children and adults [64]. It is not used to diagnose autism. It comprises 4 subscales: speech, language, and communication; sociability; sensory and cognitive awareness; and health and physical behavior. The maximum score is 179, with higher scores indicating autism of increased severity. The sensitivity and specificity of the Chinese version of the ATEC total scale and its subscales have been determined to range from 0.922 to 0.987 and 0.803 to 0.887, respectively; the scale has also been determined to have high reliability [65].

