## Discussion

This study aims to assess the effects of parent-delivered TTM in children with autism by evaluating changes in symptoms and physiological parameters (ie, gait and HRV). In practice, massage has previously been used to treat autism. However, this treatment has not been included in evidence-based practice for autism due to the lack of long-term, extensive scientific research to supports its use. At present, studies of interventions have mainly focused on qigong massage and tui na massage. Furthermore, we found that outcome measures in most prior studies were based on questionnaires and scales evaluated before and after the intervention, and that there was a lack of studies that explored the mechanisms that underlie core symptom improvement. Presumably, massage adjusts the body and mind via sensory processes [70,71] and neural and hormonal regulation (eg, changing oxytocin levels).

In comparison with prior work, this will be the first RCT to explore parental TTM in terms of its physiological and psychological effects on children with autism. We will use objective indices to investigate possible mechanisms underlying the observed effects. Our study may highlight the value of complementary and alternative therapies for adjunctive treatment of autism to enhance family-based interventions. Both parents and blinded teachers will be evaluated for effects that might cause bias. Finally, the variability of massage manipulation by parents was minimized by expert training, examinations, and supervision.

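### The correlation cut-offs are printed without an absolute value, and the test named for research question 3 has no stated adjustment for group, which matters if the arms are pooled

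*Protocol article*

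**What the plan says.** The Data Collection, Management, and Analysis section of the protocol article gives the method in one sentence: "The relationship between physiological effects and ATEC results will be evaluated using a correlation test". It then grades the result: "A coefficient value <0.4 indicates a low degree of correlation", and "a value between 0.4 and 0.7 indicates a medium degree of correlation, and a value >0.7 indicates a high degree of correlation between variables". No absolute value is written. The section does not say whether raw scores or changes are correlated, how a change would be signed, or whether the data come from both arms together or from each arm separately. Group is a stated term only in the generalized estimating equations model for ATEC.

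Two other places fix the expected direction. On ATEC, under Primary Outcome Measurement: "The maximum score is 179, with higher scores indicating autism of increased severity". On HRV, under Prior Work: "an increase in HRV reflects a state of relaxation due to parasympathetic activity induced by TTM"; that section presents this as the route to fewer restrictive-repetitive behaviours and better gait.

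The question to be answered, also under Prior Work, is: "Is ATEC score improvement related to observed changes in physiological parameters". The Discussion adds the purpose: "We will use objective indices to investigate possible mechanisms underlying the observed effects".

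**The concern.** There are two separate weaknesses.

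- **The grade depends on an unstated sign convention.** If treatment works as the authors suppose, HRV rises while ATEC falls, so the coefficient between them in native scoring is negative. A cut-off of less than 0.4 on the signed coefficient puts every negative value in the lowest grade, however strong the association.
- **A plain correlation cannot separate a link within children from a shared treatment effect if both arms enter it.** In this design the two can come apart. Parents deliver the massage, so they know the allocation, and they also rate ATEC. The HRV Measurement section describes the recording as taken after massage, a condition that controls do not share. Parental expectation could lower ATEC and acute relaxation could raise HRV with no connection between them in any individual child. A pooled correlation would still tend away from zero.

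At stake are the answer to research question 3 and any reading of it as evidence on mechanism. The comparison of ATEC between groups is not at stake.

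**Working it through.** **Inputs from the article.** Total N = 48, allocated 1:1; 80% power; two-sided 5%; 10% dropout; cut-offs 0.4 and 0.7; higher ATEC is worse; higher HRV is favourable.

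**Assumptions.** The article gives no difference or SD, so its 48 cannot be reproduced directly. Solving backwards, a standardised difference d = 0.87 gives n per arm = 2(1.96 + 0.842)²/0.87² = 20.7, so 21. Then 21/0.9 = 23.3, so 24 per arm and 48 in all. I use d = 0.87 for scale only. It belongs to ATEC, and applying it to HRV or gait is a further assumption. The value d = 1.2 is a larger illustrative case with no source in the article.

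**Step 1: the grading rule.**

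| r, native ATEC scoring | Rule as printed | Rule on absolute r, or ATEC improvement coded positive |
|---|---|---|
| -0.3 | low | low |
| -0.5 | low | medium |
| -0.7 | low | medium |
| -0.9 | low | high |

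The two-sided P value is the same in both columns, because changing the sign of one variable changes only the sign of r.

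**Step 2: pooled arms, no association within arms.** With equal arms, unit within-arm SD and a shift of d in both variables (in opposite directions), the expected pooled correlation is

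|r| = (d²/4)/(1 + d²/4).

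- d = 0.87: d²/4 = 0.189, so |r| = 0.189/1.189 = 0.16.
- d = 1.2: d²/4 = 0.36, so |r| = 0.36/1.36 = 0.26.
- To reach |r| = 0.4: d²/4 = 0.4/0.6 = 0.667, so d = 1.63 on both variables.

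At N = 48, |r| must exceed 0.285 for P < .05. Simulation with N = 48 and zero within-arm correlation (at least 20,000 trials per row) gives:

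| d on both variables | Pooled, P < .05 | Pooled, absolute r ≥ 0.4 | Adjusted for group, P < .05 |
|---|---|---|---|
| 0 | 4.9% | 0.5% | 5.0% |
| 0.5 | 7% | 0.7% | 5.0% |
| 0.85 | 18% | 3.5% | 5.0% |
| 0.87 | 19% | 4% | 5.1% |
| 1.0 | 28% | 7% | 5.2% |
| 1.2 | 47% | 16% | 4.9% |

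Adjusting for group brings the error rate back to nominal in every row.

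**Step 3: precision of a graded coefficient.** The Fisher interval is tanh(atanh(r) ± 1.96/√(n - 3)), with atanh(0.4) = 0.424.

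- n = 22 (one arm after 10% dropout): -0.03 to 0.703.
- n = 24 (one full arm): -0.00 to 0.692.
- n = 43 (both arms after dropout): 0.11 to 0.625.

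An observed 0.4 is therefore compatible with low and medium at each of these sizes. It touches high only at n = 22, by 0.003.

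**The case against.** Four objections deserve an answer.

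- **Degree of correlation ordinarily means magnitude.** Research question 3 also speaks of ATEC improvement; if that is coded as a reduction, the expected sign is positive and the rule works as printed. This stands. A reader might infer that the expected association is always graded low, but that needs native ATEC scoring together with a literal reading. Nor would research question 3 necessarily be answered wrongly, since the test of association does not depend on the label. What remains is that the methods text fixes no coding, so the grade turns on an unstated choice.
- **Nothing says the arms are pooled.** The preceding sentence on paired tests concerns changes within each group, and research questions 2 and 3, unlike question 1, do not mention the control group. A within-arm correlation has no artefact of this kind. Such detail may also sit in a fuller protocol or analysis plan that is not shown. This stands too, so the second part is conditional on pooling and is not an error found in the text.
- **The artefact is modest.** At 0.87 SD the pooled coefficient would usually be graded low by the article's own rule. That is correct; the harm there is mainly a nominally significant P, not a medium or high label. It would also be too strong to say that an observed 0.4 generally spans all three grades, since this happens only at n = 22.
- **The article is already cautious.** It sets out to explore the relationship and speaks of possible mechanisms. That is fair, and the change of description requested here is small.

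**Conclusion.** The point holds in limited form. The printed cut-offs are wrong as a rule for signed coefficients: with ATEC in its native direction, a strong favourable HRV association is literally graded low. This is a wording defect with no effect on the P value.

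Separately, the only method named for a question tied to mechanism is a correlation test with no stated adjustment for group. If the arms are pooled, and if treatment shifts both variables by 0.87 SD, the expected spurious |r| is about 0.16 and about 18-19% of trials would be nominally significant, against about 5% after adjustment. At an assumed 1.2 SD on both, |r| is about 0.26. These sizes rest on assumed effects, zero within-arm correlation and normal data. Effects of 0.5 SD or less would make the problem small (7%).

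The documents do not show that the arms will be pooled or that a false mechanism will be reported. The analysis is secondary.

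**What to change.** 1. Apply the cut-offs to |r|, and state the coding, for example that ATEC change is signed so that positive means improvement. State the favourable direction of each HRV and gait parameter as well.
2. Estimate the association as the partial correlation of ATEC change with HRV or gait change, adjusted for group. Equivalently, regress ATEC change on the physiological change plus group. Report a 95% CI beside any grade.
3. Describe the result as an exploratory association, not as evidence of mechanism.

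The cost is a few words in the methods, one model per parameter and one degree of freedom (45 instead of 46 at N = 48). No new data are needed. The article reports that data collection was complete and analysis had not begun, so the change could be made before the results are seen.
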